### Study population and recruitment process

Twenty eligible subjects will be conveniently sampled from the available FMS population currently registered at the Tygerberg Hospital (TBH) Rheumatology clinic and/or attending the monthly FMS group meetings held at the TBH Occupational therapy (OT) department. The rheumatologists and/or occupational therapist working in the TBH Rheumatology clinic and/or OT department will be asked to identify all new or previously diagnosed FMS patients attending the clinic. The principle researcher and research assistant(s) will approach all potential patients personally or telephonically, and invite them to participate in the study. In addition, the clinic's patient database will be manually searched for all potential patients who have been diagnosed with FMS, but no longer attend the monthly meetings or the clinic. All potential patients listed on the database for whom contact details are available will be contacted telephonically and invited to participate in this project.

### Study outcomes

Study outcomes will include subjective and objective measures. Subjective measures will include pain catastrophizing, as measured using the Pain catastrophizing scale (PCS) and fear-avoidance behaviours/kinesiophobia, as measured using the Tampa scale of Kinesiophobia (TSK). The *PCS is a self-report measure which includes 13 items about the thoughts and feelings experienced when an individual is in pain. Respondents use a 5- point rating scale (where 0 = never to 4 = always), to indicate how often they experience each thought/feeling. The total score for the PCS equals 52, with a score above 24 indicating a high score. High internal reliability (alpha coefficient for total pain catastrophizing scale = 0.87) has been reported in patients with chronic pain with adequate validity and test-retest reliability *[12]. *The TSK is a self-report instrument designed to assess fear of pain and activity. It consists of 17 items each rated on a 4-point Likert scale. The total score for the TSK equals 68. Responses are summed to create a total score, with higher scores (above 37) indicating greater fear of pain and activity. The scale has demonstrated test-retest reliability and internal consistency (Cronbach alphas have ranged 0.68 to 0.80) in studies of patients with chronic low back pain. Stability over time and the criterion validity and construct validity has been previously established *[22].

Objective measures will include neurophysiological changes, as measured using the Siemens MAGNETOM Allegra 3 Tesla fMRI scanner available at the CUBIC facility. *The Allegra 3 Tesla fMRI scanner is a dedicated brain scanner and currently the most advanced brain imaging instrument on the market *[23].

### Subject inclusion and exclusion criteria

Adult male and female subjects aged 18 years and older, who have been clinically diagnosed with FMS according to the American College Rheumatology (ACR) criteria [24] by a qualified rheumatologist; subjectively display high PCS (more than 24 points) and TSK (more than 37 points) scores, and are registered as a patient at TBH Rheumatology clinic/OT department, will be included in this study. Subjects diagnosed with other conditions not related to FMS i.e. cancer; who have severe physical disabilities; who suffer from chronic rheumatoid conditions i.e. systemic lupus erythmatosus and rheumatoid arthritis; who have previously been hospitalized for a major psychiatric disorder; who have an uncontrolled endocrine or allergic disorder; who are using medication other than the prescribed pharmacologic agents for FMS symptoms; who have been using any narcotics long-term; who currently or who have previously abused any illicit substances or alcohol; have been diagnosed with epilepsy, or other conditions contraindicated in the use of visual exposures to stimuli; who display any contraindications which prohibit the use of fMRI, i.e. cardiac pacemakers, metal implants, claustrophobia, pregnancy and cochlear implants; and who are unable to discontinue intake of anti-depressants 4 weeks prior to commencement of study, will be excluded from this study.

### Allocation to study groups

On consenting to participate in this project, subjects will be randomly allocated into Group A (VRET/intervention group) or Group B ("waiting list"/control group) using a computer-generated random number sequence constructed by an independent statistician. Allocation will be concealed in opaque envelopes containing the letters 'A' or 'B' and administered by an independent individual not part of the study. Study procedures will be thoroughly explained to each subject. Sociodemographic forms, the General Practice Physical Activity Questionnaire (GPPAQ), and the Revised Fibromyalgia Impact Questionnaire (FIQR) will be administered to each subject at the beginning of study 1. *GPPAQ is a validated screening tool for use in primary care to assess adult (16 - 74 years) physical activity levels *[25]. *It provides a simple 4-level physical activity index, categorizing patients as inactive, moderately inactive, moderately active and active. The FIQR is an updated version of the Fibromyalgia Impact Questionnaire (FIQ) that has good psychometric properties, can be completed in less than 2 minutes and is easy to score. It has scoring characteristics comparable to the original FIQ, making it possible to compare past FIQR results with future FIQR results *[26]. *The FIQR assesses level of functioning. The original FIQ was developed and validated by Burckhardt et al (1991) to assess the current health status of women with FMS *[27].

Study groups will progress as a cluster group from study 1 to study 2 to reduce the period of time between baseline scans and final post-intervention/control scans.

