## Methods

Ethical approval for this study was obtained from the Health Research Ethics Committee of the Stellenbosch University during July 2010. Permission to conduct the study at the various study centres was granted by the various departmental heads. All eligible subjects will be required to read and sign an informed consent form before participating in this study. A unique study identification number/code will be allocated to subjects as they are entered into the study, thereby maintaining anonymity of all study participants. Confidentiality of participant's information will be maintained throughout the study process by storing the study data in a locked facility accessible only to the study personnel.

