### Study procedures

***Study 1: ***A neurophysiological analysis (fMRI scan) will be scheduled at a time most convenient for Group A and B subjects. Transport/remuneration for transport will be provided to and from the study venue on the day of the subject's scheduled appointment. On the day of the scheduled neurophysiological analysis, subjects will again be informed of the fMRI procedure and asked to comply with all the regulations of the laboratory. This preparation session will be conducted in the MRI simulation room situated within CUBIC facility. A set of the PCS and TSK will be administered prior to the commencement of the fMRI session and used as baseline data. Subjects will be escorted to the MRI room and asked to lie down inside the fMRI chamber. Foam cushions will be used to immobilize the head. The subjects will be required to wear MRI compatible earmuffs for communication with the experimenter and to minimize scanner noise. For structural localization, a MEMPRAGE structural sequence with a spatial resolution of *1 × 1 × 1 mm^3 ^*will be acquired (approx 9 minutes) for each subject. The tasks/stimuli used in the MRI sequence have been derived from other cognitive-behavioural therapy studies [15-17], but have been modified for application in this study. The tasks/stimuli have been specifically and carefully chosen and designed so as to elicit pain catastrophizing in the FMS subjects. The tasks/stimuli, although different, are also somewhat similar in concept/idea, so that they do not elicit completely different neurophysiological activity responses. The following tasks/stimuli will be applied during the fMRI scanning: 1) Visuals of exercise/physical activities (30s clips of various exercise activities) (4 minutes); 2) Visuals of everyday sedentary activities (i.e. 30s clip of reading a book/magazine) (4 minutes); and 3) Verbal visualization (30s of standardized verbal instruction where subject is instructed to imagine an activity i.e. running, cycling, skipping, etc.) (4 minutes). The fMRI sequence which entails the application of the three tasks/stimuli will last approximately 12 minutes and consist of 3 runs. The application of each of the three tasks/stimuli will constitute one run. Each run will last approximately 240 seconds (s) and comprises of: 4 × 30s 'off' periods (no stimulus) and 4 × 30s 'on' periods (stimuli). The order of the stimuli/'off' periods will be randomized using a coin-tossing procedure. In total, from preparation to completion, the MRI procedure for each subject will last approximately 40 minutes (15 minutes preparation + 9 minutes MEMPRAGE scan + 12 minutes MRI task ± 4 minutes extra).

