
***Study 2: ***On completing baseline scans in study 1, group B subjects (n = 10) will be instructed to complete another set of the PCS and TSK and continue daily activities as normal for the next eight weeks (control group). No other education/treatment/information will be given to group B subjects. Appointments to return to CUBIC for final scans after eight weeks will be scheduled for group B subjects. On completing baseline scans in study 1, one-hour long sessions will be scheduled for group A subjects (n = 10) twice a week for eight weeks (intervention group). During the twice weekly treatment sessions, subjects will be placed in an isolated room and be exposed to visuals of various exercise activities. Visual exposure to exercise activities will be delivered via a VR head-mount display (HMD); namely the eMagin Z800 3DVISOR linked to an ASUS K61IC series laptop. The eMagin Z800 3DVISOR has a highly sophisticated built-in head tracker which allows the user six degrees of freedom in motion [28]. The HMD is placed on the head of the user, blocking off the surrounding environment. The visuals relayed to the HMD via a connected laptop are viewed on two 3D OLED 0.59 inch micro displays, which to the user seem to play as huge as a 105-inch screen. These specific features of the eMagin Z800 3DVISOR enhance the immersion of the user into the virtual environment [28]. Software will consist of an hour-long DVD comprised of various simulated exercise activities. The subject may only be accompanied by a research assistant or translator. The PCS and TSK will be administered before and after each session. Information relating to the feasibility and logistics of the study will be collected from Group A's subjects at the end of the eight-week treatment program.

The PCS and TSK will be administered before and after the eight week time period for both groups. No PCS and TSK scores will be collected during the eight weeks for group B's subjects. At the end of the eight-week study period, both groups will undergo final fMRI scans.

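### Subjects are randomised at consent, before the designated baseline questionnaires and scan, which allows avoidable losses after randomisation; the envelope should be opened after the baseline scan

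*Protocol article*

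**What the plan says.** The order of events has to be put together from several sections of the protocol article.

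- **Consent** (opening of Methods): "All eligible subjects will be required to read and sign an informed consent form before participating in this study".
- **Randomisation** (Allocation to study groups): "On consenting to participate in this project, subjects will be randomly allocated into Group A". An independent statistician makes the sequence, and an independent person administers opaque envelopes.
- **First scan** (Study procedures, Study 1): the appointment "will be scheduled at a time most convenient for Group A and B subjects". The group labels already exist, and no maximum interval from consent is given.
- **Baseline scores** (same section): "A set of the PCS and TSK will be administered prior to the commencement of the fMRI session and used as baseline data".
- **Separation of the arms** (Study procedures, Study 2). For the control arm the article states: "On completing baseline scans in study 1, group B subjects (n = 10) will be instructed to complete another set of the PCS and TSK". For the intervention arm it states: "On completing baseline scans in study 1, one-hour long sessions will be scheduled for group A subjects".
- **Antidepressants** (Subject inclusion and exclusion criteria): those "who are unable to discontinue intake of anti-depressants 4 weeks prior to commencement of study, will be excluded from this study". The start of the study is not tied to consent, allocation or any visit.
- **Movement between studies** (Allocation to study groups): "Study groups will progress as a cluster group from study 1 to study 2", with the aim of shortening the time between the two scans.

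**The concern.** Allocation comes before every measurement that the article designates as baseline. Between the two lies a period of unstated length in which a subject can drop out, miss the appointment, or prove unable to tolerate the scanner. Claustrophobia is an exclusion, but the simulator preparation takes place on the scan day, after allocation, so intolerance may first show there.

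Such a subject has been randomised but has no designated baseline, so the paired comparison in the Statistical analysis section cannot include them. The groups compared would then no longer be the groups randomised, or a replacement would have to be added after allocation. Had the envelope stayed closed until after the scan, the same subject would simply have been replaced beforehand.

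The antidepressant criterion may add to this. If the drug is stopped only after consent, the 4 weeks fall between randomisation and baseline, and a failed withdrawal becomes another loss after randomisation.

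**Working it through.** The article gives no figure on this point to reproduce, so the check is mainly one of sequence.

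**1. Order as written.** Eligibility, consent, randomisation, interval of unstated length, baseline PCS and TSK, baseline scan, then eight weeks of VRET or waiting list.

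**2. Does anything before the scan need the allocation?** Study 1 is described as an observational within-subject study (Description of the overall project), and both groups have the same scan session. The first procedures that differ are the extra questionnaire set for Group B and the session booking for Group A, both after the baseline scan. No step before that uses the letter in the envelope, except that scan booking refers to subjects by group.

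**3. What is left for a subject lost in the interval?** The entry thresholds (PCS above 24, TSK above 37) imply that screening scores exist. They are not the scores designated as baseline, and there would be no baseline scan. The Loss to follow-up section keeps data whatever the number of sessions completed, but keeping data does not supply a missing baseline.

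**4. Size per loss.** Inputs: 20 subjects (Study population and recruitment process) and 10 per group (Study procedures, Study 2). One loss is 1/10 = 10% of an arm. In SD units, the standard error of a between-arm difference is sqrt(1/n1 + 1/n2). The losses below are an assumed range of 0 to 4, because the article gives no rate:

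| Subjects per arm | Standard error | Change |
|---|---|---|
| 10 v 10 | sqrt(0.2000) = 0.447 | reference |
| 9 v 10 | sqrt(0.2111) = 0.459 | +2.7% |
| 9 v 9 | sqrt(0.2222) = 0.471 | +5.4% |
| 8 v 10 | sqrt(0.2250) = 0.474 | +6.1% |
| 8 v 8 | sqrt(0.2500) = 0.500 | +11.8% |

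**5. Length of exposure, under conditions.** Take a subject who must stop an antidepressant, does so after consent, and is allocated on the day of consent. Randomisation to final scan is then at least 4 + 8 = 12 weeks. With allocation straight after the baseline scan it is about 8 weeks. The difference is calendar time for that kind of subject only. It does not measure how many losses would be avoided.

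**The case against.** **Withdrawal as an entry criterion.** It is listed among the exclusions beside pacemakers and pregnancy, and the article speaks of eligible subjects giving consent. Read in that order, someone unable to stop is screened out before allocation. This largely stands. A reader might infer that the plan places the 4 weeks after randomisation, but the text does not say so. It leaves the anchor open, and the other reading has its own difficulty: a drug would be stopped for the study before signed consent. The sequencing point does not depend on which reading is right, because allocation precedes baseline either way.

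**Subjects without any PCS or TSK.** A reader might infer that a subject lost early has no scores at all. The entry thresholds imply otherwise. What is missing is the designated baseline set and the scan.

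**Handling of ineligible randomised subjects.** No passage says that they are removed, and their analysis normally belongs in the full protocol or SAP. That is fair, and no omission is claimed there. The point concerns the order that the article itself fixes.

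**Bias.** No difference in loss between the arms is shown, so no bias is shown. This stands. A reader might also suspect that subjects know their group when they complete the baseline questionnaires. The article does not say when they are told, so that is not part of this point.

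**Cluster progression.** Groups may have been formed early so that scans and sessions could be organised by group. This has some force: opening each envelope straight after that subject's scan could disturb the arrangement. It is met by opening envelopes together once a cluster's baseline scans are complete. The stated purpose, a short interval between scans, does not require allocation before the first of them.

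**Conclusion.** The point holds in a limited form. The article fixes allocation before the designated baseline, with no limit on the interval and no stated benefit, and so allows losses after randomisation that a later envelope would avoid.

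The number of such losses is unknown and may be zero, since the article gives no rates of non-attendance, scan intolerance, antidepressant use or failed withdrawal. Each loss costs 10% of an arm. The effect on precision is modest over the assumed range; the stronger reason for the change is to keep the randomised groups intact in a study of twenty. The contribution of antidepressant withdrawal is conditional on its taking place after consent. This is a cheap improvement, not a flaw that undermines the trial.

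**What to change.** - **Allocation to study groups:** replace allocation at consent with a rule that the envelope is opened only after signed consent, any antidepressant withdrawal, and the baseline PCS, TSK and scan, and before the procedures that differ by group. Open the envelopes together once a cluster's baseline scans are complete, so that cluster progression is kept. The statistician's sequence and the opaque envelopes stay unchanged.
- **Study procedures, Study 1:** schedule the first scan for all consented subjects instead of for subjects named by group.
- **Subject inclusion and exclusion criteria:** count the 4 weeks back from the subject's first fMRI scan.

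No questionnaire or scan is added. Some consented or scanned subjects may drop out before allocation and need replacing, at the cost of a scanner slot where the scan has been booked or done. Study 2 sessions can be booked only after the scan, but the article already books Group A's sessions at that point.

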### Study procedures

***Study 1: ***A neurophysiological analysis (fMRI scan) will be scheduled at a time most convenient for Group A and B subjects. Transport/remuneration for transport will be provided to and from the study venue on the day of the subject's scheduled appointment. On the day of the scheduled neurophysiological analysis, subjects will again be informed of the fMRI procedure and asked to comply with all the regulations of the laboratory. This preparation session will be conducted in the MRI simulation room situated within CUBIC facility. A set of the PCS and TSK will be administered prior to the commencement of the fMRI session and used as baseline data. Subjects will be escorted to the MRI room and asked to lie down inside the fMRI chamber. Foam cushions will be used to immobilize the head. The subjects will be required to wear MRI compatible earmuffs for communication with the experimenter and to minimize scanner noise. For structural localization, a MEMPRAGE structural sequence with a spatial resolution of *1 × 1 × 1 mm^3 ^*will be acquired (approx 9 minutes) for each subject. The tasks/stimuli used in the MRI sequence have been derived from other cognitive-behavioural therapy studies [15-17], but have been modified for application in this study. The tasks/stimuli have been specifically and carefully chosen and designed so as to elicit pain catastrophizing in the FMS subjects. The tasks/stimuli, although different, are also somewhat similar in concept/idea, so that they do not elicit completely different neurophysiological activity responses. The following tasks/stimuli will be applied during the fMRI scanning: 1) Visuals of exercise/physical activities (30s clips of various exercise activities) (4 minutes); 2) Visuals of everyday sedentary activities (i.e. 30s clip of reading a book/magazine) (4 minutes); and 3) Verbal visualization (30s of standardized verbal instruction where subject is instructed to imagine an activity i.e. running, cycling, skipping, etc.) (4 minutes). The fMRI sequence which entails the application of the three tasks/stimuli will last approximately 12 minutes and consist of 3 runs. The application of each of the three tasks/stimuli will constitute one run. Each run will last approximately 240 seconds (s) and comprises of: 4 × 30s 'off' periods (no stimulus) and 4 × 30s 'on' periods (stimuli). The order of the stimuli/'off' periods will be randomized using a coin-tossing procedure. In total, from preparation to completion, the MRI procedure for each subject will last approximately 40 minutes (15 minutes preparation + 9 minutes MEMPRAGE scan + 12 minutes MRI task ± 4 minutes extra).

***Study 2: ***On completing baseline scans in study 1, group B subjects (n = 10) will be instructed to complete another set of the PCS and TSK and continue daily activities as normal for the next eight weeks (control group). No other education/treatment/information will be given to group B subjects. Appointments to return to CUBIC for final scans after eight weeks will be scheduled for group B subjects. On completing baseline scans in study 1, one-hour long sessions will be scheduled for group A subjects (n = 10) twice a week for eight weeks (intervention group). During the twice weekly treatment sessions, subjects will be placed in an isolated room and be exposed to visuals of various exercise activities. Visual exposure to exercise activities will be delivered via a VR head-mount display (HMD); namely the eMagin Z800 3DVISOR linked to an ASUS K61IC series laptop. The eMagin Z800 3DVISOR has a highly sophisticated built-in head tracker which allows the user six degrees of freedom in motion [28]. The HMD is placed on the head of the user, blocking off the surrounding environment. The visuals relayed to the HMD via a connected laptop are viewed on two 3D OLED 0.59 inch micro displays, which to the user seem to play as huge as a 105-inch screen. These specific features of the eMagin Z800 3DVISOR enhance the immersion of the user into the virtual environment [28]. Software will consist of an hour-long DVD comprised of various simulated exercise activities. The subject may only be accompanied by a research assistant or translator. The PCS and TSK will be administered before and after each session. Information relating to the feasibility and logistics of the study will be collected from Group A's subjects at the end of the eight-week treatment program.

The PCS and TSK will be administered before and after the eight week time period for both groups. No PCS and TSK scores will be collected during the eight weeks for group B's subjects. At the end of the eight-week study period, both groups will undergo final fMRI scans.

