### Description of the overall project

The proposed project will consist of two interlinked experimental studies: Study 1 and Study 2.

**Study 1 **will incorporate an observational within-subject study design and aims to ascertain the neurophysiological changes occurring in the functional brain areas associated with pain catastrophizing when catastrophizing FMS patients are exposed to various visuals of exercise activities. Functional magnetic resonance imaging (fMRI) will be used to observe these neurophysiological changes within the associated functional brain areas. Study 1 will be conducted at the Cape Universities Brain Imaging Centre (CUBIC) situated at the Stellenbosch University's Tygerberg medical campus in Cape Town, South Africa (SA).

**Study 2 **will incorporate a quasi-, within-subject/between-groups experimental (pre- and post-, with/without treatment) study design and aims to ascertain the preliminary efficacy of visual exposure to exercise activities on pain catastrophizing in FMS patients. Clinical improvement in pain catastrophizing will be measured using objective and subjective outcome measures. The feasibility of using visual exposure to exercise activities as a treatment for pain catastrophization experienced by FMS patients in terms of: 1) time taken to administer; 2) ease of use; 3) safety of administration; 4) participant acceptability; and 5) participant opinion/thoughts of the intervention, will also be ascertained. Study 2 will be conducted at the Body in Motion analysis lab at the Stellenbosch University's Tygerberg medical campus in Cape Town, SA.

It is envisaged that the data collection period of the project will commence in June/July 2011 and be completed by September/October 2011.

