### Data collection and storage

The research assistant will document the randomized order of the stimuli/'off' periods during each run for each subject on a simple datasheet. This information will be blinded from the rest of the research team. Neurophysiological changes occurring during the fMRI sequence will be recorded and standard MEMPRAGE and EPI BOLD sequences will be acquired. fMRI data for each subject will be saved and stored on two hard-drives, under the reference number allocated to that subject. A research assistant will administer and collect completed PCS, TSK, GPPAQ and FIQR questionnaires, as well as sociodemographic forms from subjects. Data collected will be stored in the subject's respective folders. Back-up files of all data will be made and stored in a separate location. Folders, data and back-up data will be stored in a locked room with controlled access at all times. All subject identification and information will be kept confidential.

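### Study 2 compares a VRET session program with a waiting list, so a PCS/TSK difference cannot be credited to the exercise visuals in particular

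*Protocol article*

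**What the plan says.** The Abstract (Methods) and the section Description of the overall project give Study 2 one efficacy question: it "aims to ascertain the preliminary efficacy of visual exposure to exercise activities on pain catastrophizing in FMS patients". The Statistical analysis section compares mean PCS and TSK scores between the groups, and within subjects, to judge preliminary efficacy. The Discussion says that proof-of-concept for a VRET program will be either confirmed or ruled out.

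Study procedures, Study 2, sets out the two conditions. For the intervention group, "one-hour long sessions will be scheduled for group A subjects (n = 10) twice a week for eight weeks (intervention group". In these sessions "Visual exposure to exercise activities will be delivered via a VR head-mount display (HMD", in an isolated room, and "The subject may only be accompanied by a research assistant or translator". Also, "The PCS and TSK will be administered before and after each session"; under Data collection and storage, "A research assistant will administer and collect completed PCS, TSK, GPPAQ and FIQR questionnaires".

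Group B is told to carry on with its usual activities for eight weeks, and "No other education/treatment/information will be given to group B subjects". It has the baseline scan and the final scan, with PCS and TSK before and after the period and none in between. Study outcomes describes both PCS and TSK as self-report instruments.

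**The concern.** The aim names one ingredient, the exercise visuals. The arms differ in that ingredient and also in things that come with being treated: regular appointments, a research assistant giving questionnaires at each session, and knowing that one is in the treatment group and not on a waiting list. Self-reported scores of catastrophizing and fear of movement can respond to attention and expectation.

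The rationale in the Background and Discussion is specific: repeated viewing of feared exercise activities should reduce the fear attached to them. If PCS or TSK fell because of attention or expectation, the plan as worded would read the fall as support for that mechanism and as a reason to develop the program further. The comparison cannot tell the two explanations apart.

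**Working it through.** **What differs between the arms over the eight weeks** (Study procedures; Data collection and storage)

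| | Group A | Group B |
|---|---|---|
| Study sessions | 2 × 8 = 16 | 0 |
| Scheduled session hours | 16 × 1 = 16 | 0 |
| Session-based PCS/TSK sets, given by a research assistant | 2 × 16 = 32 | 0 |
| Exercise visuals in sessions | yes | no |
| Study visits at baseline and week 8 | yes | yes |
| Knows it is being treated | yes (inferred from open allocation) | knows it is waiting |

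Staff contact in Group A follows from the questionnaire administration. Accompaniment during the viewing is permitted but not required, so I do not count it.

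**Why analysis cannot repair this.** Write the expected between-group difference in PCS change as

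Δ = c + s,

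where c is the effect of the exercise content and s is the joint effect of attention and expectation. Every Group A subject receives both and no Group B subject receives either. There is one contrast and two unknowns, so Δ is estimable but c is not. This holds for any sample size and any model, so an unseen analysis plan could not resolve it.

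**Illustration of size.** The article gives no SD, expected effect, alpha or power, so there is no stated figure to reproduce. Everything below is assumed except n = 10 per arm.

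- Test: two-sample t test, two-sided alpha 0.05, df = 10 + 10 − 2 = 18. The Statistical analysis section names a paired t test and a Pearson correlation, not this test.
- True content effect c = 0; non-specific effect s = d SD.
- Noncentrality = d × √(10/2) = d × √5.
- Probability of a significant result in favour of VRET, from the noncentral t distribution:

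| d (assumed) | Noncentrality | Probability | Excess over 2.5% |
|---|---|---|---|
| 0 | 0 | 2.5% | – |
| 0.2 | 0.45 | 6.2% | 3.7 points |
| 0.3 | 0.67 | 9.3% | 6.8 points |
| 0.5 | 1.12 | 18.4% | 15.9 points |

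Counting both tails gives 7.1%, 9.7% and 18.5% for d = 0.2, 0.3 and 0.5, which is consistent. These figures show how such a comparison behaves. They do not estimate what will happen in this trial.

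**The case against.** The strongest reply is that the design is openly declared and the claim already hedged. The Abstract and Allocation to study groups call the control a waiting list, efficacy is called preliminary, the benefit is put only as a possibility, and a waiting list is a recognised control at this stage. This is fair, and it is why no change of design is asked for. But the word preliminary limits the strength of the evidence. It does not change what the effect is attributed to, and the aim still names the exercise visuals.

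A second reply is that proof-of-concept does not rest on PCS and TSK alone. fMRI is repeated in both groups, and the scan task has separate runs with exercise and sedentary clips. That contrast bears on content and is less open to reporting bias. It stands as a partial answer for the project as a whole, but it does not make the PCS/TSK difference specific.

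A third is that expectation is inferred, since the article does not report what subjects are told to expect. That is so. The inference is sound, because the groups are an overt treatment and a waiting list and the procedures are explained to each subject.

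Three stronger readings are tempting, and the document does not support them.

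- **Headset use is a confounder.** The Background defines VRET as immersion through a head-mounted display, so the headset is part of the treatment under test.
- **Group B has no contact at all.** It attends the baseline and week-8 visits and completes questionnaires at both. What it lacks is sessions in between.
- **Group B alone is barred from outside care.** A reader might infer this from "No other education/treatment/information will be given to group B subjects", together with recruitment from patients "attending the monthly FMS group meetings held at the TBH Occupational therapy (OT) department". The sentence describes what the study supplies. It does not forbid outside care or the meetings. A background-care instruction for both arms, or a log of other treatment, is detail that an article commonly leaves to the full protocol.

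**Conclusion.** The point holds in a limited form. A PCS/TSK difference between the groups would support the statement that the eight-week VRET session program did better than a waiting list. It would not show that exposure to exercise visuals was the active component, because that component coincides completely with 16 sessions, staff contact and knowledge of treatment, and the outcomes are self-reported. This follows from the stated arms and needs no numerical assumption.

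How often the wrong component would be credited is unknown. The illustrative increase of about 4 to 16 percentage points rests on assumed non-specific effects of 0.2 to 0.5 SD and on a test and alpha that the article does not name. The trial can run as designed; the statement of what it can conclude should be narrowed.

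**What to change.** In the Abstract, Description of the overall project, Statistical analysis (Study 2) and Discussion, define the PCS/TSK comparison as the eight-week VRET program versus waiting list. Suggested text:

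> The between-group comparison of PCS and TSK estimates the effect of the eight-week VRET session program compared with a waiting list. A difference will not by itself be taken as proof-of-concept that exposure to exercise visuals is the active component, because the groups also differ in attention and expectation. A content-matched control is left to a later trial.

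The change needs no extra subjects, visits or procedures and leaves the analysis as it is. Its cost is a narrower efficacy claim.
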